## 7.2. Doses and treatment regimens

### Dosing schedule:

#### AmBisome® monotherapy:

- Adapted from WHO recommendations for co-infected patients:  
40 mg/kg total dose: IV infusion of 5 mg/kg on day 1-5, 10, 17, 24.

#### AmBisome® in combination with Miltefosine:

- AmBisome®: 30 mg/kg total dose: IV infusion 5 mg/kg on day 1, 3, 5, 7, 9, 11.
- Miltefosine: every day during 28 days.  
The dose is calculated according to the patient weight:
  - ≤ 25 Kg, the patient receives 50mg (i.e. 1 x 50mg capsule) per day.
  - > 25Kg, the patient receives 100mg (i.e. 2 x 50mg capsules) per day.

Miltefosine capsules should be taken with meals.

Dosages of 2 capsules per day should be divided into 2 individual doses to be taken in the morning and evening. In the event the patient vomits within 1 hour of a dose, that dose should be repeated. In the event of repeated vomiting the patient should be withdrawn from that treatment allocation and treated with rescue medication.

## 7.3. Drugs labelling, packaging

Commercially available products will be used as all drugs have been registered for VL. Trial specific labeling will be applied prior to use.

## 7.4. Accountability

All study medications must be kept in a locked room that can be accessed only by the appropriate study personnel. The study medications must not be used for other purposes other than this protocol. Under no circumstances the investigator or site staff may supply study medications to other investigators or sites, or allow the medications to be used other than as directed by this protocol without prior authorization from DNDi. Adequate records on receipt, use, return, loss, or other disposition of medication must be maintained.

## 7.5. Storage

*AmBisome®*: The product should be stored at 25°C or below, not frozen or exposed to light. The shelf life is 3 years. Once reconstituted, chemical and physical in-use stability has been demonstrated for 24 hours at 25+/-2°C in vials exposed to ambient light. This is increased to 7 days if stored at 2-8°C. However to avoid contamination, once reconstituted, the product should be stored at 2-8°C and be used within 24hours.

*Miltefosine*: The product should be stored in the original package and protected from moisture. The shelf life is 4 years. Packaging should be undamaged prior to use.

## **7.6. Blinding and procedures for unblinding**

This is an un-blinded study.

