## **2.2 Study Endpoints**

### **2.2.1 Primary Endpoint**

The primary endpoint is initial parasitological cure at day 29 and is defined as absence of parasites in tissue aspirate at day 29.

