### **3. Study design and study design rationale**

#### **3.1. Study design**

This will be a randomized, parallel arm, open-label clinical trial to assess the safety and efficacy of the combination of Ambisome® plus miltefosine and Ambisome® alone for the treatment of VL in HIV co-infected patients in Ethiopia.

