### Laboratory assessment

Parasitological assessment will be done at baseline and at day 29; it will also be done at day 58 for patients who have an extended treatment. During the follow-up, it will only be performed when clinically indicated. It will be a spleen aspirate or a bone marrow aspirate if the spleen is not enlarged. Aspirates are smeared on slides, stained and graded according to the standard logarithmic criteria as defined in the below table:

| Count Oil Immersion x 100 |                                |
|---------------------------|--------------------------------|
| 6+                        | > 100 parasites per field      |
| 5+                        | 10-100 parasites per field     |
| 4+                        | 1-10 parasites per field       |
| 3+                        | 1-10 parasites per 10 fields   |
| 2+                        | 1-10 parasites per 100 fields  |
| 1+                        | 1-10 parasites per 1000 fields |
| 0                         | 0 parasite per field           |

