### **10.6. Efficacy Analysis**

The primary and secondary endpoints have been described in section 2.2.

The primary endpoint (day 29) analysis will be defined as follows:

- Treatment success: absence of parasites on day 29; hence no rescue medication provided up to this time-point.
- Treatment failure: presence of parasites at day 29 *or* requirement of rescue medication due to lack of clinical improvement/ response *or* withdrawn from the study (e.g. due to a treatment limiting adverse event/ patient absconded) *or* death.

The data will be analysed as proportions according to an intention to treat and per protocol analysis for each treatment arm.

The secondary endpoint (12 months post treatment) analysis will be defined as follows:

- Treatment success: treatment success at day 29 or at day 58 in case of extended treatment and patient being alive and disease free (absence of signs and symptoms of VL or if symptomatic, a negative parasitological assessment by tissue aspirate) at day 390.
- Treatment failure: presence of signs of symptoms of VL, confirmed by presence of parasites in a parasitological investigation. It is mandatory that all patients who have possible presence of the disease have a parasitological assessment (a spleen aspirate or a bone marrow aspirate if the spleen is not palpable).

The primary endpoint will be analyzed following Whitehead (1983) including point and interval estimation of the proportion cured in each treatment arm.

Additional analyses will be conducted to evaluate potential differences in response to treatment between relapse versus primary VL cases, and patients that have previous exposure to ART or not. This will be done at the final sequential analysis (when we reach 66 per arm) and after one year follow up. A detailed description will be included in the statistical analysis plan.

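### The protocol declares the study un-blinded and makes no exception for the slide reading that decides the primary endpoint; coded slides would be a cheap safeguard

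*Protocol*

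**What the plan says.** - Section 3.1: "This will be a randomized, parallel arm, open-label clinical trial". Section 7.6 on blinding is the single sentence "This is an un-blinded study". It does not separate open treatment from open outcome assessment.
- Section 2.2.1: "The primary endpoint is initial parasitological cure at day 29 and is defined as absence of parasites in tissue aspirate at day 29".
- Section 8.3, Laboratory assessment: "Aspirates are smeared on slides, stained and graded according to the standard logarithmic criteria as defined in the below table". Grades run from 0 to 6+. Grade 1+ is "1-10 parasites per 1000 fields", and grade 0 means cure. The section does not say who reads the slides, what the reader knows, or whether there is a second or central reading.
- Section 10.6: "Treatment success: absence of parasites on day 29; hence no rescue medication provided up to this time-point". Death, withdrawal and rescue for lack of clinical response also count as failure.
- Section 10.1 and the Synopsis (Statistics): each arm is tested alone, in a triangular test with p0 = 0.75, pa = 0.90, α = β = 0.05 and groups of 10, up to 66 patients per arm and 7 analyses.
- Section 12 covers case report forms, source documents, monitoring and data entry, but not slide reading. The sealed envelopes in section 6 conceal allocation only up to randomisation.

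**The concern.** Open treatment is understandable here, since one arm has infusions only and the other has infusions plus capsules. Open outcome reading does not follow from it. At the line between 0 and 1+, the call can rest on a handful of organisms in a long search. How long the reader searches, and how a doubtful form is called, can be influenced by knowing the arm or that the patient looks well. The result also has consequences: under the Synopsis (Study Duration) and section 7.9, a positive slide leads to a further full course or to rescue.

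The design does not dilute such an error. Each arm is compared with a fixed 75%, and section 1 (Rationale) states that there is no comparator arm. Under-reading common to both arms therefore does not cancel; it moves each arm towards the upper boundary. At stake is the conclusion that a regimen can be considered for compassionate use.

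**Working it through.** **Step 1: reproduce the plan's maximum sample size** (inputs from section 10.1).

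- θ = ln[pa(1 − p0) / (p0(1 − pa))] = ln[(0.90 × 0.25) / (0.75 × 0.10)] = ln 3 = 1.0986
- a = (2/θ) ln(1/(2α)) = (2/1.0986) × ln 10 = 4.192; c = θ/4 = 0.2747
- V = n p0(1 − p0) = 0.1875n; Z = S − 0.75n, where S is the number cured
- Correction for groups of 10: 0.583 × √(10 × 0.1875) = 0.798, so a′ = 4.192 − 0.798 = 3.394
- Upper boundary Z = a′ + cV; lower boundary Z = −a′ + 3cV. They meet at V = a′/c = 12.36, so n = 12.36/0.1875 = 65.9, which is 66 patients and 6.6 groups, hence 7 looks. This agrees with the plan. Without the correction the maximum would be 81.4.

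**Step 2: error rate with perfect reading.** Exact binomial recursion through looks at 10, 20, …, 60 and 66, rejecting when Z reaches the upper boundary, gives a probability of 0.040 of declaring adequate efficacy at true p = 0.75 (0.041 if the last look is at 70).

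**Step 3: add reading error.** Let b be the share of parasite-positive slides read as negative. The documents give no value, so 5%, 10% and 20% are assumptions. The apparent cure rate is 0.75 + b × f, where f is the share of all patients who fail on the slide.

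- f = 0.25 if every failure is slide-based.
- f = 0.25 − 0.08 = 0.17 if 8 points are deaths. The 8% is the mortality in primary VL in the historical Abdurafi series (section 1, current treatment modalities in Ethiopia; 5% in relapse cases). Applying it here is also an assumption.

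| b | Apparent rate, f = 0.25 | False 'adequate' | Apparent rate, f = 0.17 | False 'adequate' |
|---|---|---|---|---|
| 0 | 0.750 | 4.0% | 0.750 | 4.0% |
| 5% | 0.7625 | 6.0% | 0.7585 | 5.3% |
| 10% | 0.775 | 8.8% | 0.767 | 6.9% |
| 20% | 0.800 | 17.9% | 0.784 | 11.5% |

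With the last look at 70, the f = 0.25 column becomes 4.1%, 6.1%, 9.1% and 18.4%.

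**Step 4: sensitivity.** At a true rate of 0.70 with all failures slide-based, the probability is 0.65% with perfect reading, 2.0% at b = 10% and 5.5% at b = 20%. In the other direction, suppose over-calling lowers an apparent 90% to 85%, that is, 5/90 = 5.6% of negative slides called positive. The chance of declaring adequacy then falls from 0.892 to 0.521 under the same boundaries.

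**The case against.** The strongest reply is that this rests on silence. A statement that the study is un-blinded most naturally describes treatment. No section says that the microscopist knows the arm, and slide labelling may be governed by a laboratory procedure that is not shown. That stands as a limit on the wording: a reader might infer that slides were in fact read with knowledge of the arm, and the protocol does not say so. It supports only that section 7.6 makes no exception and section 8.3 supplies none.

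Second, the endpoint is fairly objective: presence or absence on a standard count scale. The protocol also gives staff reason to search carefully, since section 3.3 treats a positive test of cure as a risk factor for relapse. This bears on the likely size and direction of bias, which are unknown. It does not remove the judgement between 0 and 1+.

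Third, failures by death, withdrawal or rescue are beyond the reader's influence. This stands, and is why the f = 0.17 column is shown. Withdrawals and rescue would lower those figures further.

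Fourth, hiding arm and clinical status does not remove optimism applied to every test-of-cure slide, which is the shift modelled above. This also stands. The visit would need to be hidden too, and the table is not an estimate of what masking would save.

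Finally, a reader might extend the concern to the heterogeneity test in section 10.9. That test looks for treatment-by-stratum interaction. A reading bias tied to arm need not create one unless it also differs by stratum, and nothing in the documents shows that it would.

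**Conclusion.** The point holds as a worthwhile, cheap improvement. The protocol leaves the reading behind its one decision endpoint without any stated masking, in a design where shared under-reading is not offset by a control. Under the assumed error rates, the per-arm false-positive rate at a true 75% rises from 4.0% to between 5.3% and 17.9%. The lower end has 5% misreading and 8 points of deaths; the upper end has 20% misreading and every failure slide-based.

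A reader might take these figures as the trial's actual error rate, or conclude that its results are invalid. The documents support neither: they give no misreading rate, the direction of any bias is unknown, and at a true cure rate of 70% the error stays near or below the nominal 5% for misreading up to 20%. Who reads the endpoint and what they know is a matter of trial conduct, so it is not something to leave to the analysis plan.

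**What to change.** Amend sections 7.6 and 8.3 to say that:

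- treatment is open, but reading of the tissue aspirate is masked;
- screening, day-29 and day-58 slides carry only a code, held by someone who does not read slides;
- the existing microscopist reads them, intermixed where feasible, without knowledge of arm, clinical status or, where feasible, visit;
- results are decoded and released promptly for patient care.

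Including screening slides matters because coding only the test-of-cure slides would still tell the reader what each slide is for. Intermixing may be only partial: 132 patients over at least 18 months (section 3.2) is at most 132/18 = 7.3 enrolments a month across both sites.

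The cost is the labour of coding and code-holding at two sites; the documents give no figure for it. No extra aspirate is needed, and sample size, boundaries and treatment rules are unchanged. Masking will not correct sampling error or the limited sensitivity of microscopy.

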## **7.7. Concomitant medications**

Conditions such as malaria and respiratory tract infections should be treated prior to VL treatment if identified early enough. Exclusion of such common conditions should be undertaken for all VL patients prior to commencement of treatment. However it is expected that some patients may require management of such common conditions during study treatment.

Patients will be started on antiretroviral medication according to the Ethiopian National Guidelines (standard regimen: tenofovir, lamivudine and efavirenz (TDF-3TC-EFV) as soon as their condition permits and the ART adherence sessions have been completed; i.e. normally after 2-4 weeks. Those who are already on ART will continue the same regimen throughout the study, unless there is a clinical indication to change. Some patients will use other ART regimens, with zidovudine instead of tenofovir or nevirapine instead of efavirenz. These regimens will not be changed unless there is a clinical indication to do so.

Cotrimoxazole preventive therapy (CPT) is indicated for all HIV infected patients according to the Ethiopian National Guidelines; those who are not yet on CPT will be given cotrimoxazole 480 mg bd as soon as they are able to take oral medication.

## **7.8. Secondary prophylaxis**

Secondary prophylaxis of monthly pentamidine (4mg/kg IM) will be offered to all patients that clear parasites independently of when this is achieved (i.e. initially cured on day 29, extended treatment cured on day 58 or relapse patient that achieved cured at any point in time). Patients will be eligible for the secondary prophylaxis if their CD4 count is < 200 cells/mL and there is no contraindication (e.g. renal failure, diabetes mellitus, known hypersensitivity) for the drug used. Secondary prophylaxis will normally be continued till the patient has sufficient CD4 recovery.(i.e. over 200 cells/mL at day 390 assessment). Prophylactic treatment can be continued after the study end (day 390) if required. However, it would be stopped in case of relapse, adverse events requiring discontinuation of medication or if the patient requests to stop the prophylaxis.

The prophylaxis will be started one month after the end of the treatment and will be dispensed every month up to a maximum of 18 months.

At each of the monthly visit the glucose level will be monitored. Moreover, liver and kidney function will be performed at day 210 and 390 assessments.

## **7.9. Rescue medication**

Patients will be given rescue medication for the following reasons:

- positive test of cure at day 29 and patient unwell
- failure to respond to the extended treatment at day 58
- relapse during follow-up period

The attending physician has discretion to give rescue medication.

Any patients who receive rescue medication at any point will be considered a treatment failure.

## **8. Study Assessments**

### **8.1. Timing of Assessments**

Baseline assessments will be carried out within 7 days before VL treatment starts.

Assessments will be timed at day 1, 3, 10, 29, 58, 86 (for extended treatment only), 210 and 390 and will include clinical, parasitological, haematological, biochemical assessments.

A table with scheduled events is listed under section 5.

Assessments on day 58 (86 for extended treatment only), 210 and 390 post treatment will require some flexibility on dates due to patient travel, visit windows for each will be as follows- for day 58/86 (+/- 10 days); day 210 (+/- 1 month) and day 390 (+/- 2 months).

### **8.2. Baseline Assessments**

Baseline assessments will include anthropometric, clinical and laboratory evaluations.

### **8.3. Assessment of Efficacy**

#### **Clinical assessment**

The clinical evaluation will involve measuring temperature (axillary), spleen size, liver size, body weight at screening, on day 3, 10, 29 and at all follow-up assessments (i.e. 58, 86, 210 and 390 days).

Height will be measured at baseline only.

The size of the liver will be measured in the midclavicular line for its total span; the spleen size will be measured from the left costal margin on the anterior axillary line to the tip of the spleen medially.

## Post-kala-azar dermal leishmaniasis (PKDL)

Patients will be monitored closely for post-kala-azar dermal leishmaniasis (PKDL) through the course of the study. Diagnosis will be made clinically based on the typical appearance and distribution of the rash. Presence of PKDL will be noted at screening, day 29 and during follow-up assessments on day 58, 210 and 390.

Grading will be noted during the assessment times as follows:

- mild (Grade 1)
- moderate (Grade 2)
- severe (Grade 3).

A patient with grade 1 PKDL has lesions mainly on the face and head, with others scattered on arms, chest and back. In grade 2, the upper part of the chest and arms are also affected. In grade 3, lesions may be found on the whole body.

Patients who develop severe grade 2 or grade 3 or have mucosal and/or eye involvement (any grade) will require treatment with rescue medication at the discretion of the attending physician.

When PKDL occurs while the patient is still receiving study medication, the study medication will be continued. If at day 29 assessment, a patient has severe grade 2 or grade 3 PKDL or PKDL with mucosal and/or eye involvement (any grade), these patients will receive rescue treatment and will be considered treatment failures.

### Laboratory assessment

Parasitological assessment will be done at baseline and at day 29; it will also be done at day 58 for patients who have an extended treatment. During the follow-up, it will only be performed when clinically indicated. It will be a spleen aspirate or a bone marrow aspirate if the spleen is not enlarged. Aspirates are smeared on slides, stained and graded according to the standard logarithmic criteria as defined in the below table:

| Count Oil Immersion x 100 |                                |
|---------------------------|--------------------------------|
| 6+                        | > 100 parasites per field      |
| 5+                        | 10-100 parasites per field     |
| 4+                        | 1-10 parasites per field       |
| 3+                        | 1-10 parasites per 10 fields   |
| 2+                        | 1-10 parasites per 100 fields  |
| 1+                        | 1-10 parasites per 1000 fields |
| 0                         | 0 parasite per field           |

## 8.4. Assessment of Safety

### Clinical Assessment

The clinical evaluation will involve measuring pulse rate, blood pressure at screening, on day 3, 10, 29 and at all follow-up assessments.

## **Laboratory examinations**

Blood will be analyzed for haemoglobin, WBC, RBC, platelets at screening, on day 3, 10, 29, 58 (for patients with negative parasitology at day 29 - done only if clinically indicated), 86 (extended treatment – done only if clinically indicated), 210 and 390. Urea, creatinine, and liver function (AST, ALT, bilirubin) tests will be performed at screening, on day 3, 10, 29, 58 (for patients with negative parasitology at day 29: done only if clinically indicated). Urea, creatinine and liver function will also be mandatorily be performed at day 210 and 390 assessments, if the patient receives the secondary prophylaxis.

## **Response to ART**

CD4 count will be measured at baseline, on day 29 and on day 58 (86), 210 and 390. The analysis will be performed at the local lab of each of the two sites.

The HIV viral load will be measured during screening, on day 210 and 390. A 0.5 mL plasma sample will be collected and stored at -20°C and shipped to the Amhara region Regional Laboratory, at Bahir Dar for analysis.

### **8.5. Follow up assessments**

All patients will undergo 3 follow-up assessments at day 58, (day 86 - extended treatment only), 210 and 390 post initial treatment independently of their outcome (i.e. patients initially cured at day 29, patients receiving extended treatment and/or rescue treatment).

### **8.6. Other assessments**

#### **Measurement of immunoglobulins and cytokines**

Immunoglobulins and cytokines will be measured in plasma by ELISA. A 3 ml EDTA blood sample will be collected at screening and on day 10, 29, 210, 390 for measurement of immunoglobulins (IgG [total and IgG 1-4 subtypes], IgM, IgA, IgD and IgE levels) and cytokines ( IL-2, IL-4, and IL-10 and gamma-interferon).

The samples will be collected at Gondar site only. A minimum of 15 patients/arm will be included up to 30 patients/arm.

A 6.5 mL blood sample will be stored at the trial sites at -20°C and shipped and analyzed as a batch at the Department of Immunoparasitology, Addis Ababa University.

#### **Microarray**

As the study of any multifactorial phenomenon, and of a complex co-infection such as HIV-VL in particular, may be too complex a challenge to address using conventional single-or-limited parameter experimental setups, we aim to perform genome-wide transcriptome/microarray analysis, which maps the expression of all genes in the human genome in a single experiment. This will allow us to reliably identify and validate biomarkers for specific modes of disease progression and/or

therapy response and to generate novel hypotheses on the pathogenesis of HIV/VL co-infection. Based on published data and ITM experience, we will particularly focus on:

- a) Factors associated with the Th1-Th2 balance. Cytokine and particularly chemokine (which are almost exclusively regulated at the level of gene expression) networks will be analysed for polarisation towards a Th1 or Th2 environment, and possible causative factors for this polarisation will be mapped.
- b) Factors which are indicative for bacterial translocation from the gut to the periphery and consequent immune activation (e.g. the sCD14-TLR4-TNF axis), which may result from both HIV- and/or VL-induced damage to the gut mucosa. Such immune activation would go a long way towards explaining the observed incomplete restoration of anti-VL immune responses: due to chronic overstimulation, lymphocytes remain exhausted and cannot mount an adequate anti-VL response.
- c) Factors which are indicative of increased myeloid-derived suppressor cell activity (such as the iNOS, NADPH oxidase and arginase-1 effector molecules and HIF1a, STAT3 and C/EBP $\beta$  transcription factors), an immune suppressive cell type which is well-documented in cancer biology and which has been shown to be induced in animal models of VL. Induction of a dominant MDSC population could effectively prevent the immune system from coming fully online under ART and could thus preclude complete parasite clearance during anti-VL therapy.

The samples for the microarray analysis will be collected at Gondar site only. A minimum of 15 patients/arm will be included up to 30 patients/arm. A 2.5 ml of blood sample will be collected in PAXgene tubes at screening and on day 10, 29, 210, 390. The samples will be stored at -20 °C and then be shipped and analyzed as a batch at ITM, Antwerp.

